#### Pain Catastrophising Scale

The Pain Catastrophising Scale (PCS) will be used to identify clinically significant pain catastrophising, that is, negative pain-related thoughts and distress (often described in three domains: rumination, magnification and helplessness).^56^ The PCS contains 13 items, each scored 0–4, which yields a total score ranging between 0 and 52, with higher scores indicating more pain catastrophising thoughts. A total score ≥30 suggests clinically relevant levels of catastrophising.

#### Tampa Scale for Kinesiophobia 17

The Tampa Scale for Kinesiophobia 17 provides a valid and reliable subjective rating of kinesiophobia (ie, an irrational and debilitating fear of physical movement and activity), based on 17 items.^57^ Each item consists of a statement that is linked to fear of movement, reinjury or avoidance, which the user rates on a 4-point Likert scale (strongly disagree—disagree—agree—strongly agree). Scores range from 17 to 68; higher scores indicate an increasing degree of kinesiophobia, with scores above 37 often considered to show significant fear of movement.^58^ In addition, two subscale scores are often derived (activity avoidance, centred around the belief that activity may be harmful or increase pain; and somatic focus, which reflects the belief in underlying, serious medical problems).

#### Pain Sensitivity Questionnaire

The Pain Sensitivity Questionnaire (PSQ) is a self-rating measure for pain perception which consists of 14 items describing imagined painful situations in daily life.^59^ Additionally, for baseline reference, three normally non-painful situations are interspersed among the items. The items assess different pain modalities, for example, thermal, chemical and mechanical noxious stimuli, across various body sites and are rated on an NRS from 1 (not painful at all) to 10 (worst pain imaginable). Based on the items, a total score (average rating of all 14 items) and two subscores are generated, PSQ moderate and PSQ minor (each based on average rating of 7 different items). Previous studies have shown that PSQ scores are associated with experimentally obtained pain intensity ratings and pain behaviour in healthy subjects and pain patients.^60 61^

#### ACR 2016

The ‘ACR 2010/2011’ fibromyalgia criteria^62^ have been slightly revised in 2016, and are therefore often referred to as the ‘ACR 2016 criteria’.^63^ They consist of two subscales, the Widespread Pain Index and the Symptom Severity Scale, the sum of these is referred to as the fibromyalgia severity score (FS) and has frequently been used to assess the degree of ‘fibromyalgianess’, that is, the degree of nociplastic pain components. The FS score has been identified as a robust predictor of poorer outcome following TKA and THA and a predictor of higher opioid consumption following surgery, also in individuals who do not fulfil the criteria for fibromyalgia.^64 65^

#### Chronic Pain Acceptance Questionnaire

The Chronic Pain Acceptance Questionnaire-8^66^ will be used to assess pain-related acceptance, which entails a willingness to pursue valued activities regardless of pain.^67^ The measure consists of eight items arranged on two subscales: pain willingness and activity engagement. Each item is rated on a scale from 0 to 8, yielding a full score ranging from 0 to 48. Higher scores reflect greater pain acceptance, which is associated with lower levels of psychological distress and pain interference among individuals with chronic pain.^66 68 69^

### Participant timeline

An overview of the timeline and workflow of study procedures is provided in figure 1 and online supplemental table 2.

#### The first preoperative phase of the study

Potential study participants will be identified through screening of the digital surgery planning software Orbit. Patients who are scheduled to undergo TKA or THA at the Elisabeth Hospital in Uppsala or the orthopaedic surgical department in Enköping will be given study information documents and an invitation to complete brief, initial screening questions, including the ISI. Patients who report sleep problems corresponding to ISI score >10, that is, clinical insomnia, will be contacted by telephone for more in-depth eligibility screening, including confirmation of insomnia disorder according to DSM-V criteria, and subsequently invited to a first onsite visit to the multidisciplinary pain clinic at Uppsala University Hospital, at least 8 weeks prior to surgery. During visit 1, final check of inclusion and exclusion criteria will be performed, whereafter eligible participants who decide to enter the study will provide written consent.

As shown in figure 1 and online supplemental table 2, procedures during visit 1 entail completion of questionnaires, QST, digital cognitive testing, venipuncture to obtain blood samples and initiation of actigraphy. When visit 1 has been completed, participants will be randomised to either hybrid-format CBT-I treatment or the active comparator control, SET. The intervention will be carried out over the course of 4 weeks, according to the detailed description above, in a hybrid format including digital CBT-I or SET with addition of telehealth video-sessions with a psychologist (CBT-I) or research nurse (SET).

#### The second preoperative phase of the study

When the preoperative phase of the intervention has been completed, participants will undergo a second onsite assessment, at least 4 weeks before surgery, to repeat almost all study procedures which were administered during visit 1. Actigraphy data will be downloaded, whereafter actigraphs will once again be provided to participants to collect data up until 2 weeks postoperative. Hence, objective sleep continuity data across the whole perioperative period will be obtained.

#### The postoperative phase of the study

Participants will complete questionnaires, through the REDCap (Research Electronic Data Capture)^70 71^ electronic data capture tool hosted at Uppsala University, during the first 7 PODs, to assess the acute postoperative pain trajectory, opioid consumption and recovery parameters, for example, physical function, nausea, sleep, anxiety and depression symptoms. Two weeks postoperative, actigraphs will be returned through mail. As described above, a telehealth CBT-I or SET booster session will be administered 1–2 weeks after surgery. 3 months postoperative, participants will complete a small number of questionnaires (BPI, WOMAC OA, ISI). 6 months postoperative, participants will complete the third and final on-site visit, to repeat the procedures which were performed during visit 2, with addition of testing for CPSP according to International Association for the Study of Pain (IASP) criteria. The final data collection will take place 12 months postoperative, using the same questionnaires as for the remote 3-month follow-up assessment.

### Recruitment and retention

Based on the latest annual report from the Swedish joint arthroplasty registry, our own data^72^ and the present inclusion/exclusion criteria, we can assume that two persons undergoing THA or TKA at the two operating sites might be eligible for inclusion per week. Based on our power calculation, we anticipate that the full study population could be recruited in 2–3 years. Nevertheless, recruitment to the intervention may prove challenging in the context of major orthopaedic surgery with postoperative symptom burden and substantial energy directed towards physical therapy, etc. If recruitment proves to be complicated, efforts can be made to expand inclusion to additional nearby elective orthopaedic surgical centres. Prior to the addition of any surgical centres, amendment application(s) for approval by the Swedish Ethical Review Authority will be submitted. Additionally, the mode of invitation to take part in the study, currently through a single letter, could be altered to promote recruitment. Such strategies might include reminder letters, phone calls or enhanced promotion of the study already at the first orthopaedic preoperative appointment (when the surgery is scheduled). To compensate for travel expenses and time devoted to the study, all participants will receive Kr1000 per in-person visit (ie, a total of Kr3000 for completion of three visits). The pace of recruitment will be closely monitored throughout the trial. To enhance retention, text messages will be sent, and phone calls made, to confirm dates of follow-up assessments, both for on-site visits and remote assessments. Reminders will be sent to participants who fail to reply to follow-up invitations. If a participant finds it too burdensome to complete all questionnaires or procedures at one or more follow-up assessments, the participant will be given the opportunity to continue with completion of a reduced protocol, maintaining key outcomes. Reasons for non-adherence to the interventions will be recorded.

### Randomisation sequence generation

The allocation sequence will be created via a computerised random number generator with equal probability to the interventions (1:1) within blocks by surgery type. The randomisation procedure will ensure that equal proportions of participants undergoing THA and TKA, respectively, are assigned to the two interventions.

### Concealment mechanism (allocation concealment)

Allocation concealment will be ensured using sequentially numbered, opaque, sealed envelopes, until the patient has been recruited into the trial, which takes place after the baseline assessment (visit 1) has been completed.

### Blinding (masking)

To reduce the risk of bias, investigators, outcome assessors and data analysts will be unaware (blind) of the intervention to which the trial participants have been assigned, on intervention assignment and beyond. Participants will be aware that they are assigned to an intervention for the treatment of insomnia. The consent form states that participants will be assigned at random to either CBT-I or SET, and that both interventions are used for treatment of insomnia. The programme content of the alternative treatment will not be revealed. Although there is limited information related to objectives of the trial in the consent form, participants will be blind to most objectives and study hypotheses.

### Data collection methods and data management

Data will be collected through REDCap, in paper forms (eg, some questionnaires, interviews, QST results) and in digital format (eg, cognitive testing, actigraphic assessment). Data will be transcribed from source documentation directly into a statistical programme (eg, SPSS), or, in the case of results obtained through digital cognitive testing, directly captured and converted into a statistical programme. When data are collected on paper forms, data entry will be performed locally, to enable immediate correction of missing or inaccurate data. Assessors (research nurses) will receive training to promote data quality. Prior to analyses, the lead statistician will verify that the data are in the proper format and within an expected range of values. Additionally, there will be an independent verification of a random subset of data (∼10%) to identify missing or erroneous values. During, and up until 10 years after the trial has been completed, paper forms will be stored securely in binders placed in locked file cabinets at the study site.

### Statistical methods

A comprehensive statistical analysis plan will be approved before any analyses are conducted. All analyses will be reported according to the CONSORT (Consolidated Standards of Reporting Trials) statement.^73^ The primary analyses will focus on intent-to-treat samples, but per-protocol analysis based on treatment exposure (ie, insomnia treatment compliance) will be considered as secondary. All measured variables will be assessed for distributional qualities and transformed if necessary for use in the selected statistical models. IBM SPSS V.29 will be used for the majority of analyses, though other common validated statistical software packages may also be used.

The basic design is a parallel group (Patient Group: TKA and THA), two arm (Treatment Condition: CBT-I vs education control), independent balanced analysis of variance with one or more repeated outcome measures (Time) analysed with linear mixed models (LMMs). The number of repeated measures varies by assessment; for the primary analysis of NRS scores, the individual scores will be modelled rather than calculating and comparing averages over the time points. LMMs have the advantage of using all available data to generate unbiased estimates, assuming any missing data meets the definition of missing at random. The key results are the main effects of Treatment Condition and their interaction over Time. The interactions of Patient Group with the Treatment Condition and/or with Time are certainly of interest but secondary; specifically, we are most focused on the impact of the treatment across patient groups rather than variations between patient groups at this stage of the research. However, Patient Group will be a covariate in primary analyses.

The sample size calculations are focused within the primary analyses. Specifically, the key outcomes are the changes from baseline (Visit 1) in the pain measures to post-treatment (Visit 2) and immediate postsurgery (POD1–7). Generalized linear model (GLM) simulations using data ranges based on published studies^1 28 74^ to estimate the effect sizes of the CBT-I treatment on insomnia (medium to large)^28 75^ and the impact of the reduction of insomnia on measures of pain (medium)^1 74^ suggest that samples of 63–88 are required for 80% power (α=0.05, two-tailed); these simulations considered various combinations of effects that represented a range of small (d=0.25) to medium (d=0.55) effects over the eight key outcome assessments. A total sample size n=100 (TKA, THA combined) was selected given the upper limit and some loss of follow-up. The estimated effect size is smaller than a two-point change in the NRS (0–10) which is commonly considered the minimal clinically important difference for acute postoperative pain intensity after THA or TKA.^76^ Secondary analyses examining the additional variables and time points will be identical in execution; however, the impact of CBT-I may be reduced with lower statistical power.

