#### Inclusion criteria

Patients eligible for the trial must comply with all of the following at randomisation:

Age ≥18 years.Insomnia Severity Index (ISI) score >10.Fulfil Diagnostic and Statistical Manual of Mental Disorders, Fifth Edition (DSM-V) criteria for persistent insomnia disorder.Average pain Numerical Rating Scale (NRS) score ≥4 (scale 0–10) and/or movement-related pain NRS score ≥4 after 5 min walking.Scheduled to undergo primary (first-time, ie, not revision surgery) TKA or THA due to osteoarthritis.

Note that patients who have previously undergone THA or TKA in the contralateral hip or knee joint will be considered for inclusion.

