### Primary outcome

The primary outcome measure is:

Average pain intensity (NRS 0–10) over the past 24 hours rated each morning, averaged over the first 7 postoperative days (PODs).

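### The protocol gives two primary quantities, POD1–7 pain level and change from Visit 1, and names only surgery type as a covariate, so the precision available from Visit 1 pain is not secured

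*Protocol article*

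**What the plan says.** The Primary outcome section of the protocol article defines a level, with nothing subtracted: "Average pain intensity (NRS 0–10) over the past 24 hours rated each morning, averaged over the first 7 postoperative days (PODs". The abstract agrees.

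The Statistical methods section describes a linear mixed model (LMM) on the daily ratings: "for the primary analysis of NRS scores, the individual scores will be modelled rather than calculating and comparing averages over the time points". On the contrasts of interest it says: "The key results are the main effects of Treatment Condition and their interaction over Time". After making the interactions with surgery type (called Patient Group) secondary, it adds: "However, Patient Group will be a covariate in primary analyses". No other covariate is named for the primary analyses. The section does not say whether Visit 1 pain is a response row, a covariate or absent.

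The sample-size paragraph of the same section places its calculation within the primary analyses, then uses a different quantity: "the key outcomes are the changes from baseline (Visit 1) in the pain measures to post-treatment (Visit 2) and immediate postsurgery (POD1–7". On that footing the simulations "suggest that samples of 63–88 are required for 80% power (α=0.05, two-tailed", and 100 patients were chosen to allow for loss.

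Pain is assessed before allocation. The Inclusion criteria require "Average pain Numerical Rating Scale (NRS) score ≥4 (scale 0–10") and/or movement-related pain of at least 4 after walking, and questionnaires are completed at Visit 1, before randomisation.

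**The concern.** A postoperative level and a change from baseline can be analysed to answer the same question about treatment, but they do not have the same variance. The baseline here is chronic osteoarthritis pain, and the outcome is acute pain after the joint has been replaced. It is plausible, though not documented, that the two correlate only modestly. With equal SDs, a change score is noisier than the raw level whenever the baseline-to-outcome correlation is below 0.5. Adjusting for baseline is asymptotically no less precise than either alternative under 1:1 randomisation.

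The power of a trial of 100 patients may therefore depend noticeably on a choice that the protocol states in two ways. The choice also reaches further, because the sample-size paragraph says the secondary analyses will be run in the same way.

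**Working it through.** **The plan's own figure.** For two independent means, two-sided α = 0.05 and 80% power, n per arm = 2(1.960 + 0.842)²/d².
- d = 0.55 gives 52 per arm, 104 in total.
- d = 0.25 gives 252 per arm, 504 in total.

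Neither gives 63–88. Averaging eight assessments multiplies the variance by (1 + 7ρ)/8, and 63–88 then results at d = 0.55 if ρ is about 0.55–0.83. The document states no correlation, and it does not say whether d is standardised by the SD of the raw score or of the change. The 63–88 can be neither confirmed nor refuted.

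**Inputs for the comparison.** The documents give seven daily ratings, 1:1 allocation, α = 0.05 two-sided, 80% power and d up to 0.55. The following are assumptions:
- ρ, the correlation between postoperative days: 0.5–0.7.
- r, the correlation between baseline and a single postoperative day: 0.3–0.5.
- Equal SDs. This is then relaxed to a baseline SD of k = 0.8 times the POD SD.

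**Formulas** (variance of the patient-level quantity, with single-day variance = 1):
- Level, mean of seven days: v = (1 + 6ρ)/7
- Change from Visit 1: v + k² − 2rk, which is v + 1 − 2r when k = 1
- Level adjusted for Visit 1: v − r²

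The ratio of two variances is the ratio of the sample sizes needed.

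| ρ | r | Level | Change | Adjusted | Change/adjusted | Level/adjusted | Change/adjusted, k = 0.8 |
|---|---|---|---|---|---|---|---|
| 0.5 | 0.3 | 0.571 | 0.971 | 0.481 | 2.02 | 1.19 | 1.52 |
| 0.5 | 0.5 | 0.571 | 0.571 | 0.321 | 1.78 | 1.78 | 1.28 |
| 0.7 | 0.3 | 0.743 | 1.143 | 0.653 | 1.75 | 1.14 | 1.38 |
| 0.7 | 0.5 | 0.743 | 0.743 | 0.493 | 1.51 | 1.51 | 1.18 |

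Example for the last column, first row: 0.571 + 0.64 − 0.48 = 0.731, and 0.731/0.481 = 1.52.

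**In patients.** Take d = 0.55 in single-day SD units, ρ = 0.7 and equal SDs. Total N for 80% power is:
- r = 0.3: level 78, change 120, adjusted 68.
- r = 0.5: level 78, change 78, adjusted 52.

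At N = 100 and r = 0.3, power is 0.89 for the level, 0.73 for the change and 0.93 for the adjusted analysis.

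**What the LMM does with Visit 1.** A generalised least squares calculation for an LMM with Visit 1 as a response row gave the same variances.
- If the arm means at Visit 1 are free, the contrast from baseline is a change score.
- If they are constrained equal, the variance is that of the adjusted analysis.
- If Visit 1 is left out, the variance is that of the level.

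**The case against.** A reader might infer that the trial will analyse change scores and so throws away the precision in baseline pain. The documents do not support that.
- The primary outcome is defined as a level, the abstract agrees, and the LMM is on individual scores. The change wording stands only in the sample-size paragraph.
- The sentence on Patient Group is not a closed list. It follows a remark that interactions with surgery type are secondary, and surgery type is also the blocking factor in the randomisation. Nothing excludes Visit 1 pain.
- A statistical analysis plan is to be approved before any analysis. It may name further covariates, so the short list here is not a fault in itself.
- An LMM with Visit 1 as a row and equal arm means would recover the whole gain.

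The size is also open to challenge. If baseline pain has a narrower spread than postoperative pain, the change-score penalty shrinks: the ratio is 1.18–1.52 at k = 0.8. At r = 0.5 with equal SDs, change and level have the same variance, so subtraction adds nothing. The ratio of 1.78 for level against adjusted needs r = 0.5 with ρ = 0.5. That is a correlation of 0.5/√0.571 = 0.66 with the seven-day mean, which is hardly modest. Nor can a restricted range of average pain be taken for granted, because a patient can enter on movement-related pain alone.

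All of this stands, and it limits the point. It does not remove the disagreement between the outcome definition and the sample-size paragraph, which a later analysis plan cannot undo for a sample size already set. Nor does it show that the stated plan obtains the gain: nothing in the text points to a baseline row with equal arm means.

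**Conclusion.** The point holds in a limited form. The protocol states two primary quantities, and on its own wording neither secures the precision available from Visit 1 pain, although neither rules it out.

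The possible loss is largest if the change wording governs: about 1.5–2.0 times the patients of the adjusted analysis with equal SDs, or about 1.2–1.5 times with a baseline SD of 0.8 of the POD SD. If the outcome definition governs and baseline is left out, the loss is smaller: about 1.1–1.2 times at r = 0.3, rising to 1.5–1.8 times at r = 0.5. These ranges rest on assumed correlations and SDs. The direction does not: adjustment is asymptotically no less precise than either alternative.

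This does not show that n = 100 is too small, because the simulations behind 63–88 cannot be reproduced from what is stated.

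**What to change.** 1. Make the raw POD1–7 NRS scores the single primary quantity, as the Primary outcome section already does, and reword the sample-size paragraph to match. State which SD standardises d and which correlations were assumed.
2. Include Visit 1 pain in the primary LMM alongside surgery type. Either enter it as a fixed covariate, optionally with its interaction with day, or keep it as a baseline row with the arm means constrained equal. Say which Visit 1 pain item is used.
3. Do the same for each secondary outcome that has a Visit 1 value.

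The cost is wording in the protocol and the analysis plan, one or a few model terms and a trivial loss of degrees of freedom. No new data are needed. The change should be made before outcome data are seen.

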### Monitoring of data and safety

Given known minimal risks associated with the interventions used, there is no need for a formal safety monitoring committee or interim analysis. To evaluate the progress of the trial and identify potential problems, the principal investigator will designate appropriately qualified personnel to periodically perform quality assurance checks. The monitor will assure that data are accurate and in agreement with any paper source documentation used, verify that participants’ written consent has been properly obtained and documented, confirm that participants entered into the study meet inclusion and exclusion criteria, verify that study procedures are being conducted according to the protocol guidelines and review any adverse events. Specifically, given that sleep restriction and stimulus control have been associated with initial increased sleepiness and fatigue, these symptoms will be assessed as part of routine monitoring. Meetings with an independent data and safety monitoring board will be scheduled if there are any serious adverse events or harms that might be considered at least possibly related to the study procedures. Adverse events will be collected after the participant has provided consent, enrolled in the study and started the intervention.

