Assessment of *fibromyalgia tender points* (according to American College of Rheumatology (ACR) 1990 criteria) through application of pressure (4 kg).Assessment of *pressure pain detection threshold* (PPDT) using a digital algometer (SBMEDIC Electronics, Solna, Sweden) with a 1 cm^2^ probe area applied to the skin at a constant rate of 30 kPa/second. The participant will be instructed to indicate (through pushing a button) when the stimulus ‘first feels painful’. Testing will be performed with the participant in a supine position. In the case of participants undergoing THA, four locations will be examined: (1) a proximal, volar area on the forearm (bilateral) and (2) the area overlying the major trochanter (bilateral). For those undergoing TKA, the locations will also include a proximal, volar forearm area, but instead of the major trochanter, an area adjacent (medial and proximal) to the femorotibial junction (ie, just above the ‘fatty pad’) will be examined (bilateral). Two trials with a 30 s interstimulus interval will be completed per area. Subsequently, pressure pain testing will be performed once in each area to ascertain which level of pressure (kPa) is required to elicit pain corresponding to NRS 4/10 (ie, PP4) and NRS 7/10 (ie, PP7), respectively.To examine *temporal summation* (TS), that is, central nervous system augmentation of pain caused by repeated painful stimulation, mechanical stimulation will be applied to three areas (THA: area overlying the major trochanter on the affected side, the contralateral area and ‘the triangle’ between the first and second metacarpal bones on the dorsum of the left hand; TKA: knee-area described above, the contralateral area and the same ‘triangle’ on the dorsum of the hand described above). A weighted pinprick stimulator (‘PinPrick’, MRC Systems GmBH, Heidelberg, Germany) calibrated to deliver 256 nM of force will first be applied to the skin in an area which will not be tested subsequently. The participant will be asked to rate how painful the stimulus is on a scale from 0 to 100 (0=no pain, 100=worst pain imaginable); if the participant perceives this stimulation to be painful, the 256 mN stimulator will be used throughout the TS testing, otherwise a 512 mN stimulator will be used. The participant will first rate how painful a single pinprick stimulus is in each of the three testing areas. Thereafter, a train of identical 10 pinprick stimuli, at a frequency of 1 per second (1 Hz), will be administered within an area of 1 cm^2^. The participant will rate the peak pain experienced during the testing sequence, whereafter TS will be calculated as peak pain rating divided by pain rating of single initial stimulus. In case the participant rates the first stimulus as 0 (ie, no pain), a minimum value of 1 will be assigned in order to enable calculation of TS. Assessment of TS will be performed twice in each area, with a 2 min pause between tests. Results from the two sets of testing will be averaged.*Conditioned pain modulation* (CPM), that is, the capacity of endogenous pain inhibitory systems, will be assessed through a QST paradigm comprising an ischaemic pain (tourniquet) conditioning stimulus and a pressure pain test stimulus (as described in detail by Tour *et al*^52^). First, PPDT will be assessed twice in a midpart area of the thigh contralateral to the hip/knee which will undergo surgery (near the crossing of the sartorius and rectus femoris muscles); subjects will also be asked to report pain intensity (NRS 0–100) in the contralateral arm. Then, a tourniquet will be placed on the contralateral arm, and subsequently inflated to constrict blood flow. The subject will then be given a 2 kg weight to perform reverse wrist curls, to elicit ischaemic pain in the left forearm and hand. Once the pain reaches a level corresponding to NRS 50/100, the investigator will repeatedly assess PPDT in the area specified above, at 30 s intervals. Maximally, eight measurements will be conducted prior to the release of the tourniquet. The subject will then be asked to rate the maximum arm pain perceived during the test, as well as pain in the hip/knee after the test. Finally, following 5 min of rest, two PPDT measurements will conclude the CPM testing session.To assess *cold pain tolerance*, a circulating, cold water bath (2°C) will be used (Somedic AB, Hörby, Sweden). Participants will first be asked to report pain intensity in their hip/knee and the contralateral hand. Thereafter, participants will immerse the contralateral hand up to the wrist in the cold water, up to an uninformed 4 min maximum time limit. Participants will be instructed to indicate when the cold first starts feeling painful (cold pain detection threshold), and to keep their hand in the water for as long as possible, until the cold pain becomes intolerable (cold pain tolerance threshold). If the participant is able to keep their hand in the water throughout the full 4 min period, the test will be aborted and the cold pain tolerance threshold assessed as 240 s. Immediately after the test, subjects will be asked about maximum pain in the hand, as well as pain in the hip/knee. Finally, after 5 min of rest, participants will once again be asked to report pain intensity in these locations.

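### Adverse-event collection opens only when the intervention starts, so the Visit 1 pain testing and blood sampling fall outside the stated rule

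*Protocol article*

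**What the plan says.** The section Monitoring of data and safety fixes when collection opens: "Adverse events will be collected after the participant has provided consent, enrolled in the study and started the intervention". The same section says that meetings of an independent data and safety monitoring board will be scheduled in the event of "serious adverse events or harms that might be considered at least possibly related to the study procedures". It plans no standing safety committee and no interim analysis, and it justifies this by the low risk of the interventions.

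The first preoperative phase of the study sets the order of events at the first on-site visit. After the final eligibility check, "eligible participants who decide to enter the study will provide written consent". Then "procedures during visit 1 entail completion of questionnaires, QST, digital cognitive testing, venipuncture to obtain blood samples and initiation of actigraphy". Allocation follows: "When visit 1 has been completed, participants will be randomised to either hybrid-format CBT-I treatment or the active comparator control, SET". The section on allocation concealment agrees, placing recruitment into the trial at a point "which takes place after the baseline assessment (visit 1) has been completed".

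The QST section describes what participants undergo. For conditioned pain modulation, "a tourniquet will be placed on the contralateral arm, and subsequently inflated to constrict blood flow", followed by weighted wrist exercise until pain reaches 50 out of 100. For cold pain tolerance, "a circulating, cold water bath (2°C) will be used", with immersion for up to 4 minutes. The battery also includes tender-point pressure at 4 kg, pressure raised until pain reaches 7 out of 10, and pinprick trains. The biomarker section adds about 24 mL of blood.

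**The concern.** A participant is exposed to research procedures from the moment of consent, but the rule waits for a later milestone. The Visit 1 tests are designed to provoke pain, in people with painful osteoarthritis who are awaiting arthroplasty. A faint, a bruise, a prolonged pain flare or a venipuncture complication at that visit has no stated place in the adverse-event record.

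Two things are at stake. The first is completeness. Someone who has a bad reaction at Visit 1 and withdraws before treatment never enters the collection window, yet is the person whose event would be most informative about procedure tolerability. The second is the safety system itself. Without a standing committee, the event-driven board meeting is the main independent safeguard described. It refers to study procedures, while the collection rule that would normally feed it leaves out their first use. The low-risk justification speaks of the interventions and does not address the testing.

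**Working it through.** No arithmetic is needed to establish the gap. It follows from setting the article's statements in time order.

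1. **Consent**: at Visit 1, after the final eligibility check (The first preoperative phase of the study).
2. **QST, venipuncture and other baseline procedures**: also at Visit 1 (same section; content in the QST and blood biomarker sections).
3. **Randomisation**: once Visit 1 is complete (same section; confirmed under Concealment mechanism).
4. **Intervention start**: necessarily after randomisation.
5. **Adverse-event collection opens**: after consent, enrolment and intervention start (Monitoring of data and safety).
6. **Visit 2**: after the intervention, repeating almost all Visit 1 procedures (The second preoperative phase of the study).
7. **Surgery, then Visit 3 at 6 months**: repeating the Visit 2 procedures (The postoperative phase of the study).

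The three conditions in step 5 are joined by a conjunction, so the latest one governs, and that is step 4. Everything in step 2 precedes it. No other part of the article opens collection earlier.

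Removing only the intervention condition would not close the gap. The concealment section places recruitment into the trial after Visit 1. If enrolment carries that meaning, the second condition also falls after the Visit 1 procedures. Of the three conditions, only consent precedes them.

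By visit count, 1 of 3 on-site visits lies outside the window (1/3 = 33%), and it is the first exposure for each of the 100 planned participants. Visits 2 and 3 lie inside it for those who started the intervention.

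**The case against.** Several points on the other side have force.

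- **The trigger has no time limit.** A reader might infer that the board trigger cannot operate for Visit 1. The text does not support that. The trigger sentence stands apart from the collection sentence, and the monitor's duty to review adverse events is also undated. A serious event seen by staff at Visit 1 would meet the trigger as worded. What remains is that nothing at Visit 1 feeds it systematically.
- **Some effects are recorded.** A reader might infer that Visit 1 harms leave no trace. In fact the QST protocol records maximum arm or hand pain and hip or knee pain after the tourniquet and cold tests. For the cold test, pain is asked about again after 5 minutes of rest. These are outcome data, and they would not capture a faint, a bruise or a delayed problem.
- **Staff would witness acute events.** Testing is done by one of two experienced research nurses. It would go too far to say that later visits proceed in ignorance of what happened at the first. An informal note is still not collection under a stated rule.
- **The 33% is only a visit count.** Visit 2 repeats almost all procedures, and the figure and supplemental table that would show which are omitted are not available here. The fraction says nothing about how many events would be missed.
- **The trial's inference is untouched.** Visit 1 precedes randomisation, so its events cannot bias the comparison of harms between arms or the primary outcome. The sleepiness and fatigue that the section singles out arise after the intervention starts and are covered.

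These points limit the weight of the concern. They do not remove it, because the late start is an explicit rule and not a detail left to a fuller document.

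**Conclusion.** The point holds as a gap in safety capture, confined to Visit 1 and the interval up to intervention start. Under the stated rule, procedure-related harms in that period are not covered, including in anyone who withdraws before treatment. That sits badly with a safety trigger worded around study procedures, and the two sentences must be reconciled.

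In size it is one of three on-site visits and the first exposure of all 100 planned participants. The document gives no event rate, so no number of missed events can be stated. The conclusion assumes that the collection sentence is applied as written and that Visit 1 runs in the order described. It does not extend to bias between the arms, nor to the same kinds of procedure at the later visits for participants who have started treatment. It is worth correcting because it is cheap and concerns safety, not because it threatens the trial's results.

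**What to change.** In Monitoring of data and safety, replace the collection sentence with one that starts adverse-event collection at signed consent, with no further condition of enrolment or intervention start. Report events before intervention start in a separate summary of all consented participants, not by arm. Report events after intervention start by arm as now intended. Add a clause stating that Visit 1 events count toward the existing trigger for independent safety review.

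The cost is one or two sentences and a small amount of extra form completion by the research nurses at Visit 1. If the change counts as substantial, it follows the amendment route the article already describes. No test procedure, intervention or efficacy analysis changes.
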